### Interventions

After the initial evaluation, 92 patients with CLBP will be randomly assigned to one of the two groups and will receive electrical dry needling (experimental group) or conventional physiotherapy (control group). All participants will receive 1 session per week for 6 weeks, until they have received a total of 6 sessions. Patients must complete 100% of their scheduled face-to-face treatment sessions, and those in the control group must also complete 80% of the home exercise sessions in order to remain in the intention-to-treat analysis.

During the study, participants can only receive their assigned treatment; they cannot combine the study treatment with medications or any other treatment. Any interference in the treatment will be grounds for exclusion. Patients may abandon the study at any time, and the assigned interventions may be suspended or modified in a particular trial patient in response to improvement or deterioration (adverse effects) of low back pain. Adverse events will be reported to the principal investigator, who will monitor the affected patients and the possible causes of these events.

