### Electrical dry needling group

Patients assigned to the electrical dry needling group (*n* = 46) will receive up to three 30-min treatment sessions (1 session per week for 6 weeks). Electrical stimulation will be applied bilaterally to the active and latent myofascial trigger points of the following muscles, following the MTrPs maps described by Travell and Simons: [2, 14] quadratus lumborum, multifidus and iliocostalis. The number of needle insertion sites will vary in each patient; the treating therapist will determine the points to be treated in each session based on whether they are active, latent or absent. Prior to needle insertion, the site will be sterilized with 70% alcohol using a cotton swab (Fig. 2).

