### Data collection

At the beginning of the study, the following demographic data will be collected: age, sex, weight, height, education and clinical presentation. Primary and secondary outcome measures will be evaluated at baseline prior to randomization to different groups. This will be followed by an immediate post-treatment assessment (1 day after the final intervention) and an evaluation 2 months after the end of the intervention (short-term follow-up).

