### Data analysis

Statistical analysis will be performed using SPSS© version 21.0 and STATA 14 using the principles of intention to treat. Comparisons will be made between the two study arms. We will calculate the difference between the groups after the final treatment session and at 2 months post-intervention (short-term results).

The efficacy variable for this clinical trial is the difference between continuous variables (i.e., RMDQ, ODI, VAS, TSK, SF-36, PSQI, HADS, pressure algometry, McQuade test and trunk range of movement) at baseline and at predetermined time points (electric dry needling treatment vs conventional physiotherapy):

The Kolmogorov-Smirnov test will be used to assess the normality of continuous variables.

The equality of means of the intragroup hypotheses will be analysed using Student’s *t* test for paired clinical variables in the case of parametric distributions and the Kruskal-Wallis *H* test in the case of nonparametric distributions.

One-way analysis of variance (ANOVA) will be used to test the intragroup hypothesis in the case of parametric distributions, and the Kruskal-Wallis *H* test will be used in nonparametric distributions.

Post hoc analysis will be obtained for parametric distributions and Mann-Whitney *U* for nonparametric distributions.

The confidence interval will be set at 95% and the level of significance at 0.05.

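### Treatment may be suspended or modified because back pain improves or worsens, yet the 100%-session rule would then drop that patient from the intention-to-treat analysis, and the assessment date of a patient who is kept is unclear

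*Protocol article*

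**What the plan says.** Three statements in the Interventions section bear on the same patient.

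- The planned course: "All participants will receive 1 session per week for 6 weeks, until they have received a total of 6 sessions".
- The exception: the assigned intervention "may be suspended or modified in a particular trial patient in response to improvement or deterioration (adverse effects) of low back pain". No criterion is given and no decision-maker is named.
- The completion rule: "Patients must complete 100% of their scheduled face-to-face treatment sessions", and this is required "in order to remain in the intention-to-treat analysis".

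The section on the electrical dry needling group adds a further difficulty about what is scheduled, since patients there "will receive up to three 30-min treatment sessions (1 session per week for 6 weeks").

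The timing of assessment is described in several places. Data collection specifies "immediate post-treatment assessment (1 day after the final intervention) and an evaluation 2 months after the end of the intervention". Data analysis compares the arms on the "difference between the groups after the final treatment session and at 2 months post-intervention". The Abstract places the first assessment at 6 weeks and counts the later one from the end of treatment. Participants counts both, at 6 weeks and 2 months, from the start of treatment. Table 1 has columns for 6 weeks and 2 months.

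**The concern.** The primary outcomes are two back-pain disability scores (RMDQ and ODI) and a pain scale (VAS). The trigger for suspending or modifying treatment is a change in low back pain. A patient's course on the primary outcome can therefore decide how much treatment is received. Through the completion rule it can also decide whether the patient is analysed at all.

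Exclusion that depends on the outcome after randomisation is what an intention-to-treat analysis is meant to prevent. If suspensions occur at different rates or for different reasons in the two arms, the remaining patients are no longer the groups that randomisation made comparable.

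If the completion rule is not applied and the patient stays in, a second question arises: on which day is the outcome read? Where the visit is counted from the last session received, its date moves with the decision to stop. The arms may then be compared at different times since randomisation.

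**Working it through.** The plan gives no figure of its own for this point, so there is none to reproduce. The check sets the passages side by side, dates a worked example, and illustrates the possible size of the exclusion effect.

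**1. What happens to a patient suspended after session 3**

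Inputs: six weekly sessions (Interventions). Assumptions: the first session is on day 0, the suspension is permanent, 2 months is about 61 days, and the Abstract's 6 weeks runs from the start of treatment.

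- Sessions delivered: 3 of 6 = 50%. Against a schedule of six, the 100% condition fails and the patient leaves the analysis.
- Session 3 falls on day 2 × 7 = 14. Session 6 falls on day 5 × 7 = 35.

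If the patient is nevertheless kept, the dates depend on the section followed:

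| Section | First assessment, full course | First assessment, stopped after session 3 | Follow-up, full course | Follow-up, stopped after session 3 |
|---|---|---|---|---|
| Data collection | 35 + 1 = day 36 | 14 + 1 = day 15 | 35 + 61 = day 96 | 14 + 61 = day 75 |
| Abstract | 6 × 7 = day 42 | day 42 | day 96 | day 75 |
| Participants | day 42 | day 42 | day 61 | day 61 |

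Data analysis uses the same anchor as Data collection (final session, end of intervention) without the one-day interval. Under Data collection both visits move 36 − 15 = 21 days earlier. Under the Abstract only the follow-up moves. Under Participants neither moves.

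**2. Possible size of the exclusion effect (illustration on assumed shares)**

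The share of patients suspended is not stated. Suppose a share s of one arm, those who improved most, is suspended and dropped, and changes are normally distributed with standard deviation σ. The mean improvement of those who remain falls by

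σ × φ(z) / (1 − s), where z is the standard normal quantile at 1 − s and φ is the normal density.

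Sample size states a standard deviation of 2.5 points, used here as the spread of change (assumption). It also mentions a variance of 10, that is √10 = 3.16, so both are shown. The target difference is 2.5 RMDQ points and each arm has 46 patients.

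| s | Patients of 46 | φ(z) | Shift, σ = 2.5 | Shift, σ = 3.16 |
|---|---|---|---|---|
| 5% | 2.3 | 0.103 | 0.27 | 0.34 |
| 10% | 4.6 | 0.175 | 0.49 | 0.62 |
| 20% | 9.2 | 0.280 | 0.87 | 1.11 |

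For s = 10% and σ = 2.5: 2.5 × 0.1755 / 0.90 = 0.49. With σ = 2.5 the shifts are about 11%, 20% and 35% of the 2.5-point target.

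If instead those who worsened most are dropped, symmetry gives a shift of the same size in the other direction. If both kinds are dropped, or both arms are affected, the shifts partly or wholly cancel. The table therefore gives a scale and does not predict a bias.

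**The case against.** Stopping or changing treatment for adverse effects is an ordinary exception to a planned course. A modified patient may still receive all six sessions on time, and a suspension may be temporary. It is therefore too strong to say that the fixed course and the exception can never both be followed. This stands. The defect is narrower: wording that covers all participants without qualification, and a 100% rule, stand beside a trigger that includes improvement and has no criterion.

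A fixed calendar is also already in the text. Participants counts both visits from the start of treatment, and one day after the final intervention may simply mean the day after the planned sixth session. This stands too, so outcome-dependent timing is not certain. The sections do conflict, however, and nothing says which applies to a suspended patient.

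A reader might infer that responders who stop early are read at a favourable moment, which would flatter their arm. The documents do not support that. Under the 100% rule such a patient leaves the analysis, and losing the best responders would lower that arm's mean improvement. The inference would need the schedule to be shortened for suspended patients, which the text does not say.

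A reader might also infer that staff who know the arm make these decisions. Treating therapists necessarily know it, and only the outcome assessor and statistician are described as blinded, but the clause names nobody.

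Finally, the lack of a log of suspensions would not by itself be a finding in a condensed article.

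**Conclusion.** The point holds in a limited form. Applied literally, the Interventions section lets a change in back pain lead to suspension and then to removal from an analysis labelled intention-to-treat. If the patient is kept, the sections disagree on the assessment date. In the example the first visit is on day 15 or day 42 and the follow-up on about day 75 or day 61, depending on the section followed.

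The 21-day shift rests on weekly sessions from day 0, a permanent stop after session 3, the final-session anchor, and retention despite the 100% rule. The shifts of 0.27 to 1.11 RMDQ points rest on assumed shares and on selective removal from one arm. How many patients would be affected is not stated, and neither the size nor the direction of any bias can be derived from the document. The inconsistency should be corrected because correction is nearly free. A demonstrated bias is not the reason.

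**What to change.** 1. Reconcile the six-session, suspension/modification and 100%-completion sentences in Interventions, together with the session count in the dry needling section. Which treatment rule stands is for the sponsor's clinicians to decide.
2. Set both assessments on one calendar, counted from randomisation or from the first session, for every randomised patient whatever sessions were received. Use the same wording in the Abstract, Participants, Data collection, Data analysis and Table 1.
3. Keep suspended or modified patients in the intention-to-treat analysis in their allocated arm. If an analysis restricted to those who completed treatment is wanted, give it its own name and present it as supplementary.
4. Report suspensions and modifications by arm, with sessions delivered and the reason.

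The cost is wording changes and one entry on the treatment record. No extra visits or patients are needed.

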### Electrical dry needling group

Patients assigned to the electrical dry needling group (*n* = 46) will receive up to three 30-min treatment sessions (1 session per week for 6 weeks). Electrical stimulation will be applied bilaterally to the active and latent myofascial trigger points of the following muscles, following the MTrPs maps described by Travell and Simons: [2, 14] quadratus lumborum, multifidus and iliocostalis. The number of needle insertion sites will vary in each patient; the treating therapist will determine the points to be treated in each session based on whether they are active, latent or absent. Prior to needle insertion, the site will be sterilized with 70% alcohol using a cotton swab (Fig. 2).

**Fig. 2 Fig2:**
[figure not shown]
Electrical dry needling group. Location and signalling of active and latent MTrP. Placement of dry needles in active and latent MTrP. Dry electrical needling technique in active and latent MTrPs. MTrP, myofascial trigger point

Two sizes of sterilized disposable stainless steel acupuncture needles will be used: 0.25 mm × 30 mm or 0.30 mm × 40 mm. The size of the needle will depend on the patient’s physical constitution (i.e. muscle and/or connective tissue thickness). The needle will be inserted until it reaches the active or latent MTrP or taut band that causes the local twitch response [41]. The needles will then be connected to an electric current and left in situ for 30 min (TensMed S82-Enraf Nonius) [42, 43]. A low-frequency current (2 Hz) will be generated by a TENS device with a moderate pulse duration (250 μs) and a continuous biphasic waveform at an intensity described by the patient as “mild to moderate” [44].

### Conventional physiotherapy group

Patients assigned to the conventional physiotherapy group (*n* = 46) will receive ischaemic compression and analytical stretching of the quadratus lumborum, multifidus and iliocostal muscles once a week for a total of 6 weeks.

Ischaemic compression will consist of constant pressure stimulation with the thumb on each MTrP for between 30 s and 2 min. This compression sequence will be repeated several times. The intensity of the pressure will be adjusted to a level at which each subject reports “comfortable pain”, in order words, between the pain threshold and the maximum tolerable pain [36, 45] (see Additional file 1 for the analytical stretching procedure).

These patients will also be given a dossier of home lumbar spine exercises to be performed 5 days a week for a total of 6 weeks (Additional file 2: dossier of home exercises). To monitor compliance, patients will be instructed to note down in a booklet the dates on which they complete the exercises in the dossier.

### Data collection

At the beginning of the study, the following demographic data will be collected: age, sex, weight, height, education and clinical presentation. Primary and secondary outcome measures will be evaluated at baseline prior to randomization to different groups. This will be followed by an immediate post-treatment assessment (1 day after the final intervention) and an evaluation 2 months after the end of the intervention (short-term follow-up).

#### Primary outcome measures

The following are the primary outcome measures:
Roland Morris Disability Questionnaire (RMDQ): This self-reported questionnaire consists of 24 items that rate limitations in different activities of daily life attributed to low back pain, such as walking, bending over, sitting, lying down, dressing, sleeping, personal care and daily activities. Disability is rated from 0 points (best) to 24 points (worst) [46].Oswestry Disability Index (ODI): The Oswestry Disability Index assesses the limitations in activities of daily living in 10 dimensions, each rated on a 6-point scale (0–5 points). The higher the score, the greater the disability. The overall score is expressed as a percentage and is used to classify people as minimally disabled (0–10%), moderately disabled (20–40%), severely disabled (40–60%), crippling back pain (60–80%) or bedridden (80–100%) [47].Visual analogue scale (VAS): Study participants will indicate the intensity of their pain on a 100-mm VAS. They are asked to situate their pain on a 100-mm horizontal line, where 0 mm indicates “no pain”, and 100 mm indicates “the worst pain imaginable” [48].

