### Sample size

The sample size was calculated according to the specifications established by Willian [59]. The calculations were based on the detection of differences of 2.5 points in the RMDQ (minimum detectable difference between means for a variance of 10 points in patients with chronic low back pain), assuming a standard deviation of 2.5 points, a 2-tailed test, an alpha (*α*) of 0.05 and a target power (beta) of 85%.

The following specifications will be considered: *α* = 0.05, statistical power of 85% and loss to follow-up of 15%. The sample size calculation yielded a total of 92 participants to be randomized to two intervention groups.

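### Three unranked primary outcomes at two visits, one 0.05 level and no success rule leave six tests open as the primary result, although the trial is sized on RMDQ alone

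*Protocol article*

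**What the plan says.** **Outcomes.** The section Primary outcome measures opens with "The following are the primary outcome measures" and lists RMDQ, ODI and VAS pain, in no stated order of importance.

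**Visits.** Data collection schedules "an immediate post-treatment assessment (1 day after the final intervention) and an evaluation 2 months after the end of the intervention". Data analysis then states: "We will calculate the difference between the groups after the final treatment session and at 2 months post-intervention (short-term results". Neither visit is designated primary.

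**Analysis.** Data analysis begins its definition of efficacy with "The efficacy variable for this clinical trial is the difference between continuous variables" and runs the three primary outcomes together with the secondary ones in one list. The only statement on error control is "The confidence interval will be set at 95% and the level of significance at 0.05". The post hoc analysis mentioned there follows the ANOVA or Kruskal-Wallis step; it is not presented as control across outcomes or visits.

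**Sample size.** "The calculations were based on the detection of differences of 2.5 points in the RMDQ", "assuming a standard deviation of 2.5 points, a 2-tailed test", with alpha 0.05, 85% power and 15% loss, giving 92 participants. ODI and VAS do not enter.

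**The concern.** Three outcomes at two visits make six primary between-arm comparisons, and nothing in the article says which one decides the trial. Two things follow.

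- If one significant result among the six is enough, the overall false-positive rate is above the level set for each test.
- If results disagree, for example VAS significant and RMDQ not, there is no pre-set reading, and the emphasis can be chosen after the data are seen.

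The trial's stated objective is comparative effectiveness, and the abstract says the results will inform clinicians on which treatment is more beneficial. The conclusion therefore depends on which comparison is treated as decisive.

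**Working it through.** **1. The plan's own figure.** With difference 2.5, SD 2.5, two-sided alpha 0.05 and 85% power, n per arm = 2(1.960 + 1.036)² × (2.5/2.5)² = 17.96, so 18. Allowing for loss, 18/0.85 = 21.2, so 22 per arm and 44 in total. With the variance of 10 given in the same section (SD 3.16), n = 17.96 × 10/6.25 = 28.7, so 29; 29/0.85 = 34.1, so 35 per arm and 70 in total. Neither gives 92. That is a separate matter. What counts here is that the calculation uses one outcome, one test and alpha 0.05.

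**2. Number of tests.** 3 outcomes (Primary outcome measures) × 2 visits (Data collection, Data analysis) = 6, each read against 0.05.

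**3. Chance of at least one false positive if any one result counts.**

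Under independence:
- either direction: 1 − 0.95⁶ = 0.265
- in favour of needling only (2.5% per test): 1 − 0.975⁶ = 0.141
- three outcomes at one visit, either direction: 1 − 0.95³ = 0.143

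The article gives no correlations, so a range was simulated (equally correlated normal test statistics, 1,000,000 draws per value):

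| Assumed correlation | Six tests, either direction | Six tests, favouring needling | Three tests at one visit, either direction |
|---|---|---|---|
| 0 (exact) | 26.5% | 14.1% | 14.3% |
| 0.3 | 24.1% | 12.1% | 13.6% |
| 0.5 | 20.7% | 10.3% | 12.6% |
| 0.7 | 16.3% | 8.1% | 10.9% |
| 0.9 | 10.8% | 5.4% | 8.4% |
| Nominal, one test | 5% | 2.5% | 5% |

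**4. The opposite rule.** If all six had to be significant, the error rate would not be inflated. Joint power, however, cannot exceed that of the weakest of the six tests. Taking the stated 85% for RMDQ at face value, it would fall below 85% unless the other five were always significant whenever RMDQ was.

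**5. What the candidate remedies need.** 92 less 15% leaves 46 × 0.85 = 39 evaluable per arm. RMDQ power = Φ(2.5/(SD × √(2/39)) − z), with z the two-sided critical value:

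| Rule | Alpha per test | RMDQ power, SD 2.5 | RMDQ power, SD 3.16 | N for 85% power with 15% loss |
|---|---|---|---|---|
| RMDQ at one visit | 0.05 | 99% | 94% | 44 or 70 |
| Bonferroni, three outcomes at one visit | 0.0167 | 98% | 86% | 58 or 90 |
| Bonferroni, all six | 0.0083 | 96% | 80% | 66 or 104 |

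A single RMDQ test fits within 92 under either SD. A six-way split does not if the variance is 10.

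**The case against.** **No any-one-wins rule is stated.** A reader might infer that the plan grants six chances of success. The article does not say so; it is silent on what counts as success. The error rates above are therefore conditional on that reading. The silence remains a fault, because both the lenient and the strict reading stay open until results are known.

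**26.5% is not the rate for a false claim that needling is better.** A reader might take it that way. It counts errors in both directions and assumes independence. Independence is unrealistic here: RMDQ and ODI both measure back-related disability, and each outcome is repeated in the same patients. The directional rates are about half as large, and at correlation 0.9 the directional figure is 5.4% against 2.5%. This objection stands as to size, but inflation remains at every correlation tried.

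**The tests are loosely described.** Data analysis labels both the paired t test and the ANOVA as intragroup, so the exact form of the between-arm test is not fixed. The same section does say that the two arms will be compared at both visits, which supports the count of six.

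**An analysis plan may settle it.** Multiplicity procedures are commonly left to such a plan, and their absence alone would not be a finding. But the choice of primary outcomes is made in this article. It fixes three without ranking and two visits without a primary one.

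**The work is partly feasibility.** Ethics and dissemination speaks of feasibility results, and the Discussion foresees a later definitive trial. That softens the need for strict familywise control. It does not remove it, given the effectiveness objective and the powered comparison.

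Sizing a trial on one of several primary outcomes is not in itself an error. It matters here because it shows which outcome the design already treats as leading.

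**Conclusion.** The point holds as a badly fixed choice of primary endpoint: three unranked outcomes, two visits, one 0.05 level and no decision rule, in a trial sized on one outcome.

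The size depends on two assumptions that the article neither states nor rules out: that any one significant result may be claimed as primary, and how strongly the six tests are correlated. Across assumed equal correlations from 0 to 0.9, the either-direction rate is roughly two to five times its nominal 5%, and the directional rate roughly two to six times its nominal 2.5%. Equal correlation is a simplification, since correlations within and between visits will differ.

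The article does not support the conclusion that the trial will be misreported, or that one particular visit is the correct primary one. This should be changed; it does not invalidate the design.

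**What to change.** Name RMDQ at one pre-specified visit as the sole primary test, at two-sided 0.05. RMDQ follows from the protocol's own sample size section, and alpha and the 92 participants stay as they are.

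Either visit cures the multiplicity. If the 2-month visit is chosen, its definition must be reconciled first. Participants times it from the start of treatment, whereas the Abstract and Data collection time it from the end. With six weekly sessions, two months (about 8.7 weeks) from the start falls only about 8.7 − 6 = 2.7 weeks after treatment finishes, so the two definitions give different endpoints.

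Make ODI, VAS and RMDQ at the other visit key secondary, and state the visit at which ODI and VAS are tested. Test them by Holm or in a fixed order, and only if the primary test is significant. Report all remaining outcomes with 95% confidence intervals and no confirmatory claims.

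**Cost.** No extra patients or assessments. ODI and VAS lose primary status. The change is more than an edit of wording. Ethics and dissemination says analyses will not be modified once enrolment has begun, and that any amendment goes to the institutional research committee and is reported with the results. It therefore has to be made before unblinding, as a documented amendment communicated and reported in that way.
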